#### GPs

The GP will maintain a record of the participants with an allocated code for each patient. This code is also marked on the questionnaires. The university only receives the patients’ codes and has no access to their names.

A questionnaire is filled out by the GPs with information on the professional characteristics (gender, age, specialty, work time) and of the organizational context, such as single or group practice, regional structures and available resources.

At T0, the GP gives information for each participating patient on demographics, clinical characteristics: comorbidities, BMI, smoking status, PYs smoking, information on respiratory symptoms cough, sputum, dyspnea and severity of dyspnea (Medical Research Council MRC dyspnea scale) spirometry (FEV1/FVC < 0.7) and grade of severity according to GOLD guidelines FEV1 > 80% GOLD I mild COPD, FEV1 50 to 80% GOLD II moderate COPD, FEV1 30 to 50% GOLD III severe COPD, FEV1 < 30% GOLD IV very severe COPD), exacerbation frequency and current (pulmonary) drug therapy.

After 12 months (T1), GPs are asked about smoking cessation counseling activities, yearly influenza vaccination and assessment of physical activity; if ‘yes’ , how was physical activity assessed? Possibilities include anamnesis and objective tests, for example, sit to stand test (STS), six-minute walking test, and ergometer. Also asked about are motivation for physical activity and referral to pulmonary rehabilitation, assessment of exacerbation frequency and health care utilization in previous year, including hospital admissions, emergency department attendances and unscheduled visits. Whether patient education activities are given, verbally and/or via patient booklet, with definition of COPD and information about the main causes, signs and symptoms of COPD is also inquired into, as is whether information on medication and using inhalation devices, face-to-face instruction and demonstration of inhalation technique is supplied. Additionally, whether information on how to identify and manage an aggravation of symptoms (exacerbation) and whether an action plan for exacerbation management, including a written medication adjustment for exacerbation treatment is supplied, is asked about. GPs are also asked whether they educate patients in the practice or refer them to an external COPD program connecting COPD patients with specialized health professionals and community resources (lung associations, support groups).

This procedure will be carried out to compare patients’ reported procedures with GPs’ self-reported performed procedures and is assessed as secondary outcome measure.

The GP questionnaires are also marked with the patient’s code and will be returned to the university in a stamped envelope. GP measurements will take place at baseline (pre-data collection) and after 12 months (post-data collection). Pre-data collection is estimated to last three months.

An independent research assistant of the university will enter the data directly into the SPSS program (version 18.0 or higher, SPSS, Chicago, IL, USA)**.**

For an intermediate outcome, we will assess mediating processes with a self-efficacy scale for professional knowledge, skills and behaviour before and right after the ‘QualiCCare’ workshop and after 12 months.

The process evaluation will also include outreach visits and interviews, which have shown to be effective strategies to support implementations in primary care. Therefore, one outreach visit will be performed eight to twelve weeks after the training workshop for GPs and practice assistants in the intervention group. The aim of this outreach visit is to assess if the structures in the practices are appropriate to perform care according to the study protocol. Furthermore, the visit aims to reveal possible problems which might have occurred, and to discuss and implement appropriate solutions. Whether the instruments are used as intended will also be checked. The outreach visit will be performed by a study nurse of the study center.

### Statistical analysis

#### Calculation of sample size

Based on available data from Switzerland [7,30], and a recently performed cross-sectional survey of our study group, we assume a mean of four regarding the number of performed indicators (primary outcomes 1 to 9 as mentioned above) and a SD of 2.3. We assume an increase in the intervention group in the mean of performed indicators of 1.5. Given a power of 90% and a significance level alpha of 5%, as well as an intracluster correlation coefficient (ICC) of 0.04, we will need eight patients per GP assuming participation of 30 GPs, resulting in 240 patients. Assuming a dropout rate of at least 20% (dropouts are possible on a GP level but also on a patient level, therefore this rate is estimated to be about 20%), we will need 288 patients.

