**Methods:**

CAROL is a cluster-randomized controlled trial with randomization on the general practioner (GP) level. Thirty GPs will be randomly assigned to equally sized intervention group or control group.

Each GP will approach consecutively and regardless of the reason for the current consultation, patients aged 45 years or older, with a smoking history of ≥ ten pack-years (PY). Patients with confirmed (by spirometric evaluation) COPD will be included in the study. GPs in the intervention group will receive ‘QualiCCare’ education, which addresses knowledge, decision-making and behavioural aspects as well as delivery of care according to COPD quality indicators and evidence-based key elements. In the control group, no educational intervention will be applied and COPD patients will be treated as usual. The study period is one year.

The primary outcome measure is an aggregated score of relevant clinical processes defining elements in the care of patients with COPD: smoking cessation counseling, influenza vaccination, motivation for physical activity, appropriate pharmacotherapy, patient education and collaborative care. Given a power of 90% and a significance level alpha of 5%, 15 GPs recruiting eight patients each will be necessary in both study arms. With an assumed dropout rate of 20%, 288 patients will need to be included.

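### On the printed inputs, 90% power needs four patients per GP (120 in total), not eight (240); the planned 240 gives about 99% power

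*Protocol article*

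**What the plan says.** All the inputs are in the protocol article under Calculation of sample size. For the score and its spread: "we assume a mean of four regarding the number of performed indicators (primary outcomes 1 to 9 as mentioned above) and a SD of 2.3". For the effect: "We assume an increase in the intervention group in the mean of performed indicators of 1.5". Power is set at 90% and alpha at 5%, without saying whether the test is one- or two-sided. The clustering input and the result, which is presented as a requirement, stand together: "intracluster correlation coefficient (ICC) of 0.04, we will need eight patients per GP assuming participation of 30 GPs, resulting in 240 patients". An allowance for 20% dropout is then added to reach 288.

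The abstract repeats the result, again at 90% power and 5% alpha: "15 GPs recruiting eight patients each will be necessary in both study arms". It also gives the allocation: "Thirty GPs will be randomly assigned to equally sized intervention group or control group". The Data analysis section names a t-test for the primary comparison.

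**The concern.** The section prints every input that a standard cluster-randomised calculation needs and states the answer as a necessity, so the answer can be checked. A standardised difference of 1.5/2.3 = 0.65 is large and an ICC of 0.04 with eight patients per GP is mild clustering. A need for 120 patients per arm looks far too high for that combination.

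This is the only justification given for the size of the trial. If the printed inputs are right, the article understates the power and presents twice the required number of patients as necessary. If the calculation used another difference, SD or ICC, one of the printed planning values misleads readers, including those who may take the ICC or SD into a later trial.

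**Working it through.** **Inputs.** Difference d = 1.5, SD s = 2.3, ICC ρ = 0.04, alpha 5%, power 90%, and 30 GPs, so k = 15 per arm. All are from Calculation of sample size except the equal split, which is from the abstract. Two readings are assumed: 1.5 is the between-group difference, and alpha is two-sided.

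**1. Without clustering.** n per arm = 2 × (1.960 + 1.282)² × (2.3/1.5)² = 49.4, so 50.

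**2. Patients per GP with 15 GPs per arm.** The design effect is DE = 1 + (m − 1)ρ. Setting 15m = 49.4 × DE and solving gives

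m = 49.4 × (1 − 0.04) / (15 − 49.4 × 0.04) = 3.64, so four per GP, or 30 × 4 = 120 patients.

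**3. Power by patients per GP**, with SE = s × √(2 × DE / (15m)):

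| Patients per GP | DE | Total | Power, normal | Power, t on 28 df |
|---|---|---|---|---|
| 3 | 1.08 | 90 | 84.5% | 81.9% |
| 4 | 1.12 | 120 | 92.2% | 90.3% |
| 8 (stated) | 1.28 | 240 | 99.4% | 99.1% |

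For the stated design, SE = 2.3 × √(2 × 1.28/120) = 0.336 and 1.5/0.336 − 1.96 = 2.51, which gives 99.4%. The article's 90% is not reproduced. Four per GP is the answer under both methods.

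**4. Difference detectable with 90% power at 240.** By the normal approximation, (1.960 + 1.282) × 0.336 = 1.09 points. With t on 28 df it is 1.13.

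**5. Do common allowances close the gap?** Power of the stated design at d = 1.5:

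| Variant | Power |
|---|---|
| One-sided 5% (normal) | 99.8% |
| Cluster-size coefficient of variation 1.0 (t, 28 df) | 97.1% |
| 20% of the 240 patients lost, 6.4 per GP (t, 28 df) | 97.7% |
| 12 GPs per arm × 8 (t, 22 df) | 96.8% |
| Rank test, efficiency 0.864 (t, 28 df) | 98.0% |

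None comes near 90%. Dropout cannot be the reason in any case, because it is added after the 240.

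**6. What single change would make 240 match 90%?**

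| Input | Printed | Needed (normal) | Needed (t, 28 df) |
|---|---|---|---|
| Difference | 1.5 | 1.09 | 1.13 |
| SD | 2.3 | 3.17 | 3.06 |
| ICC | 0.04 | 0.204 | 0.180 |

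**7. The change-score route to a larger SD.** If 2.3 is a single-time-point SD and change is analysed, the SD becomes 2.3 × √(2(1 − r)), where r is the correlation between baseline and follow-up. At r = 0 it is 3.25, and power at 240 is 88.4% (normal) or 86.2% (t). At r = 0.05 it is 3.17, with 90.0% (normal). At r = 0.12 it is 3.05, with 90.1% (t). So this route works only if r is about 0.05 to 0.12.

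**The case against.** The strongest reply is that nothing printed need be wrong, because a condensed article may have dropped a step. Two such steps are plausible.

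- The 1.5 is worded as an increase in the intervention group. If some improvement among controls was also expected, the net difference could have been near 1.1.
- The primary outcome is described as a total increase after one year, and patients answer the same questions at both time points, while the planning SD rests partly on a cross-sectional survey. A change-score SD with low correlation gives about 90% at 240.

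This stands as far as it goes. The cause cannot be settled from the article, and a missing step is as possible as a wrong number. It does not rescue the text: neither step is stated, and the printed inputs are offered as sufficient for the result.

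Three stronger readings are tempting and are not supported.

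- **That the ICC really used was about 0.20.** That value comes only from back-solving. A smaller difference or a larger SD fits equally well.
- **That the true requirement is 128 patients.** Inflating 50 per arm by 1.28 gives 64 per arm, but that means 8 GPs per arm, whereas the section fixes 30 GPs. It also has only 85.8% power with t on 14 df.
- **That the primary test has an error rate of about 20%.** For a patient-level t-test that ignores clustering, this would hold at an ICC of 0.20: 1.96/√2.40 = 1.27, about 21% two-sided. At the printed 0.04 it is 1.96/√1.28 = 1.73, about 8%. How the t-test handles clustering is a separate matter.

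**Conclusion.** The point holds as an internal inconsistency. The printed inputs require four patients per GP and 120 in total, half the stated figure. The stated 240 has about 99% power for 1.5 points and 90% power for about 1.1 points. This rests on reading 1.5 as the between-group difference, 2.3 as the SD of the analysed score, and alpha as two-sided; a one-sided test widens the gap.

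Which figure is off cannot be determined from the article. If the printed inputs are right, the discrepancy is conservative: the trial has more power than stated, and keeps about 97% to 98% after losing 20% of the 240 patients or three GPs per arm. Harm arises only if a planning value was misreported, which is possible but not shown. It should be corrected, but it does not threaten the validity of the trial.

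**What to change.** Re-run the calculation and make the sample size section and the abstract agree. Which correction applies depends on what was actually done:

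- If the printed inputs were the planning values, keep them and state that 30 GPs with eight patients each give about 99% power for 1.5 points, and 90% power for about 1.1 points.
- If another between-group difference, SD or ICC was used, print that value with its source. For a change-score SD, give the assumed correlation between baseline and follow-up. For a net difference, give the assumed change among controls.

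In either case, say whether alpha is two-sided and whether 1.5 is the difference between groups. No replacement value should be filled in by back-solving, since that could put a second wrong figure in print. The cost is restating figures in two places; the recruitment target need not change.

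### The enrolment target of 288 multiplies 240 by 1.2 instead of dividing by 0.8, so 20% dropout leaves about 230 patients, not 240; the stated 90% power is not threatened

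*Protocol article*

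**What the plan says.** The section Calculation of sample size fixes the number before dropout: "we will need eight patients per GP assuming participation of 30 GPs, resulting in 240 patients". Its inputs are as follows.

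- Mean and SD: "we assume a mean of four regarding the number of performed indicators (primary outcomes 1 to 9 as mentioned above) and a SD of 2.3".
- Effect: "We assume an increase in the intervention group in the mean of performed indicators of 1.5".
- Clustering: "intracluster correlation coefficient (ICC) of 0.04".
- Error rates: "Given a power of 90% and a significance level alpha of 5" per cent.

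The allowance for loss comes next. It opens with "Assuming a dropout rate of at least 20" per cent, notes that both GPs and patients may drop out, and ends with "therefore this rate is estimated to be about 20%), we will need 288 patients".

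The Methods part of the Abstract gives 15 GPs with eight patients each per arm and then: "With an assumed dropout rate of 20%, 288 patients will need to be included". Neither place gives any other reason for 288.

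**The concern.** Both places present 240 as the number the calculation calls for and 288 as the number to enrol so that the calculation survives dropout. If 288 are enrolled and exactly the anticipated fraction is lost, fewer than 240 remain. The allowance therefore does not do what it is there to do.

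What is at stake is the consistency of a published target. Recruitment will be monitored against 288, and planned numbers will be compared with achieved numbers. A trial that met its target and had exactly the dropout it expected would still fall short of its own declared number.

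**Working it through.** **Inputs from the article.** 240 patients before dropout; 30 GPs, 15 per arm; dropout d = 0.20; SD 2.3; difference 1.5; ICC 0.04; alpha 5%; power 90%. The article does not say whether the test is one- or two-sided. I assume two-sided, which is the more demanding choice.

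**Step 1: reproduce 288.** n × (1 + d) = 240 × 1.20 = 288, an exact match.

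**Step 2: the number that retains 240.** n / (1 − d) = 240 / 0.80 = 300. The stated target is 12 patients lower (12 / 300 = 4%).

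**Step 3: what 288 delivers.**
- Remaining after 20% loss: 288 × 0.80 = 230.4, a shortfall of 9.6 against 240 (4%).
- Largest dropout that still leaves 240: 1 − 240 / 288 = 16.7%.

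**Step 4: does the shortfall matter for power?** With N patients remaining in k practices, the average cluster size is m = N / k, the design effect is 1 + (m − 1) × 0.04, and the effective number per arm is n_e = (N / 2) / design effect. The standardised difference is 1.5 / (2.3 × √(2 / n_e)). Power is taken from the normal distribution and, more cautiously, from the noncentral t with k − 2 degrees of freedom.

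| Case | m | Design effect | n_e per arm | Power, normal | Power, t |
|---|---|---|---|---|---|
| 240 patients, 30 GPs (as stated) | 8 | 1.28 | 93.75 | 99.4% | 99.1% |
| 230.4 patients, 30 GPs (all loss at patient level) | 7.68 | 1.267 | 90.9 | 99.3% | 98.9% |
| 230.4 patients, 24 GPs (all loss is whole GPs) | 9.6 | 1.344 | 85.7 | 99.0% | 98.3% |
| 240 patients, 24 GPs (300 enrolled, all loss is whole GPs) | 10 | 1.36 | 88.2 | 99.1% | 98.5% |

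For the second row by hand: 1.5 / (2.3 × √(2 / 90.9)) = 4.40; 4.40 − 1.96 = 2.44; the normal probability is 99.3%.

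**Step 5: why so much power remains.** The same inputs need 50 patients per arm without clustering. With clusters of eight, 50 × 1.28 = 64 per arm, or 128 in total. The 240 is therefore well above what these inputs require for 90% power. That is a separate discrepancy in the sample size section, used here only to judge how much the dropout slip matters.

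**The case against.** The strongest reply is that nothing turns on the slip. The aim is 90% power, and about 230 patients give about 99% on the stated inputs, even when the loss comes as whole practices. The 240 used as the yardstick is itself not derivable from those inputs. All of this stands. It makes the point minor but does not make 288 correct: the article calls 240 needed, assumes 20% loss, and gives a target that does not retain 240.

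A second reply is that 20% may be meant as a mark-up on 240, or that the softer wording (about 20%) could stretch to 16.7%. The text calls it a dropout rate, the same sentence sets 20% as a minimum, and the Abstract gives 20% without qualification. None of these wordings fits 16.7%. If the minimum is taken literally, 230 is the most that would remain.

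Two further inferences are tempting and are not supported.

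- 288 over 30 GPs is 9.6 each, and a reader might call that impossible to recruit. It is only an average. GPs approach patients consecutively and the article sets no equal quota after the allowance, so the fraction is no evidence against 288.
- A reader might conclude that 7.7 patients per GP will remain. That holds only if every GP stays. The article expects loss of GPs as well, and if all the loss were whole GPs, 24 would remain with about 9.6 patients each.

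**Conclusion.** The dropout step is wrong as written, in both the Abstract and the sample size section. The target of 288 leaves about 230 patients after the assumed 20% loss, about 10 (4%) fewer than the 240 that the article calls for, and it covers 16.7% dropout. This part rests only on the article's own figures and on the usual meaning of a dropout rate as a fraction of those enrolled.

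A reader might go on to infer that the trial is underpowered. The article does not support that. At the stated SD, difference and ICC, with a two-sided 5% test, power stays between about 98% and 99% whether the loss falls on patients or on whole practices. These figures depend on the stated inputs being right and on roughly equal cluster sizes. The point is a low-priority correction of a stated number, not a design flaw.

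**What to change.** Correct the Abstract and the section Calculation of sample size together.

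- **Preferred:** keep 288, and say that it leaves about 230 patients after 20% dropout. Give the power for that number on the stated inputs: about 99% if all 30 GPs stay (about 7.7 patients each on average), and about 98% to 99% if the loss is six whole practices (24 GPs, about 9.6 patients each). This adds no patients and changes nothing in the design.
- **Alternative:** state 300 as the number that retains 240 after 20% dropout. This means 12 more patients. If the loss comes as whole GPs, 300 preserves the count of 240 but not the layout of 30 practices with eight patients each (24 × 10 = 240), and the text should say so.

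In either case, use one wording for the dropout rate, since a minimum of 20% and an estimate of about 20% are different assumptions.

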#### Data analysis

A *t*-test will be used for independent group comparisons in the primary outcome between control and intervention group. Each quality indicator itself can also be regarded as a binary outcome (performing a specific procedure (yes/no)). To analyze these binary outcomes separately logistic regression will be used to model the relationships between the outcome and treatment group, age and gender. Other potentially important covariates will be identified through exploratory analyses. The longitudinal aspect of the data can be incorporated into the model in various ways; we will utilize the generalized estimating equations (GEE) approach [31].

For continuous outcomes such as quality of life (QoL) instruments, repeated measures analysis of variance is appropriate [32].

Fixed effect parameters will include treatment group, age, gender, and other potentially important covariates. The primary data analysis will follow the intent-to-treat (ITT) approach where appropriate. This means that all available data from all individuals will be analyzed according to treatment group assignment, regardless of whether or not each individual actually received the assigned treatment.

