## Methods/Design

We will conduct a cluster-randomized controlled trial (randomization on GP level) with primary care physicians in the Canton of Zurich in the years 2013 and 2014.

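### The primary t-test as written ignores the randomised GP clusters, so its true type I error is about 8-9%, not 5%, at the plan's own ICC

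*Protocol article*

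**What the plan says.** The Methods/Design section describes a "cluster-randomized controlled trial (randomization on GP level"). On numbers, the abstract states: "Thirty GPs will be randomly assigned to equally sized intervention group or control group", and that "15 GPs recruiting eight patients each will be necessary in both study arms". The sample size section sets the error rates ("Given a power of 90% and a significance level alpha of 5"%) and allows for clustering through an "intracluster correlation coefficient (ICC) of 0.04".

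The Primary outcome section compares COPD patients in the two arms on what they report, and the score is built per patient from nine yes/no indicators. For this outcome the Data analysis section names one method, a t-test: "test will be used for independent group comparisons in the primary outcome between control and intervention group". The intention-to-treat paragraph of that section speaks of data from individuals.

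The single indicators are to be analysed by logistic regression. For the longitudinal aspect of the data, "we will utilize the generalized estimating equations (GEE) approach". For continuous outcomes such as quality of life, "repeated measures analysis of variance is appropriate". The listed fixed effects are treatment group, age, gender and other covariates. The Data analysis section mentions no random GP effect, no variance clustered on GP and no analysis of GP means.

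**The concern.** An independent-samples t-test on patients is valid only if the ICC is zero. The design and the sample size calculation both say that it is not. The endpoint also makes clustering likely: most of the nine indicators are things the GP does or does not do (advice, assessment, instruction, prescribing), so patients of one GP will tend to score alike.

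Ignoring this makes the standard error too small, the confidence interval too narrow and the p-value too low for the primary comparison. The direction of error is the same for any between-arm comparison of single indicators or CAT that omits the GP. The trial would claim a 5% false-positive rate that its own inputs contradict.

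This is more than a detail left to a later analysis plan. The article names a specific test that does not fit the design, and an analysis plan would have to overrule that sentence.

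**Working it through.** **Inputs from the protocol article.** 30 GPs, 15 per arm (abstract). From Calculation of sample size: 8 patients per GP, so 120 per arm and 240 in total; 288 recruited to allow for 20% dropout; ICC 0.04; SD 2.3; difference 1.5; alpha 5%; power 90%. Two-sided testing is assumed, since sidedness is not stated.

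**The plan's own figures.**
- Alpha: with ICC = 0, the patient-level t-test has a simulated type I error of 4.9%. The nominal 5% therefore holds only without clustering.
- Sample size: n per arm without clustering = 2 × [2.3 × (1.960 + 1.282) / 1.5]² = 49.4, rounded to 50. Multiplied by 1.28 this gives 64 per arm, or 128 in total. The stated 240 is not reproduced. It is matched by an ICC of 0.20: design effect 1 + 7 × 0.20 = 2.4, and 50 × 2.4 = 120 per arm. This is a separate point, but it matters here because it leaves open which ICC was used.

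**Type I error of the t-test that ignores clusters.**
- Design effect: DEFF = 1 + (m − 1) × ICC, with m patients per GP.
- True alpha = 2 × [1 − Φ(1.96 / √DEFF)].
- For m = 8: DEFF = 1 + 7 × 0.04 = 1.28 and √1.28 = 1.131. The standard error is understated by 1 − 1/1.131 = 12%. 1.96 / 1.131 = 1.732, so alpha = 0.083 and coverage is about 92%.

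| Patients analysed per GP (ICC 0.04) | DEFF | True alpha, formula | Simulated, patient t-test | Simulated, t-test on GP means |
|---|---|---|---|---|
| 7.68 (288 less 20%, over 30 GPs) | 1.267 | 0.082 | not run | not run |
| 8 | 1.280 | 0.083 | 0.084 | 0.050 |
| 9.6 (all 288) | 1.344 | 0.091 | 0.091 | 0.050 |
| 3 to 12, mean 8 (assumed spread) | – | – | 0.088 | 0.049 |

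Simulations used 60,000 trials per scenario, 30 clusters and a normal outcome.

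**Sensitivity to the ICC (assumed range, m = 8).** 0.01: 5.8%. 0.02: 6.6%. 0.05: 9.2%. 0.10: 13.3%. 0.20: 20.6% (simulated 20.8%).

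**Power of a test that respects the clusters** (t-test on GP means, 28 df, difference 1.5).
- ICC 0.04: SE = 2.3 × √(2 × 1.28 / 120) = 0.336; 1.5 / 0.336 = 4.47; power about 99%.
- ICC 0.20: SE = 2.3 × √(2 × 2.4 / 120) = 0.46; 1.5 / 0.46 = 3.26; power about 88%.

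**The case against.** The best defence is that the article never names the unit of the t-test. A t-test on GP means also compares independent groups, and a separate analysis plan may say so. This affects the certainty of the reading, not the need for a change. The score is per patient, the outcome compares patients, the analysis text refers to individuals, and averaging by GP is not mentioned. If GP means were intended, the text must say it.

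Second, GEE and the mention of fixed effects do not exclude a GP level. That is true: the clustering unit for GEE is not given. But GEE is introduced for the longitudinal aspect, in the text on binary indicators, and cannot be read as covering the primary t-test.

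Third, the size has limits, and these stand:
- The 9% end requires all 288 patients to be analysed. For the planned analysed sample the figure is about 8%.
- The ICC of 0.04 is given for the nine-indicator score only, so no figure can be attached to the single indicators or CAT. In a group-by-time test of CAT, stable GP differences cancel, and the inflation may be smaller.
- The primary outcome is worded as an increase. If change scores are tested, the relevant ICC is that of change, which is not given and could be lower or higher.
- At the planned effect the result would survive: the naive statistic is 1.5 / (2.3 × √(2/120)) = 5.05, and 5.05 / 1.131 = 4.47 after correction. At ICC 0.04 only a borderline result would change. The naive statistic would have to exceed 1.96 × 1.131 = 2.22 (naive p about 0.027), or somewhat more with 28 df.

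**Conclusion.** The concern holds, and the text must be corrected. As written, the primary test ignores the randomised unit and contradicts the ICC used for the sample size. Its true type I error is about 8% for the planned analysed sample (0.082-0.083 by formula, 0.084 simulated) and 9.1% if nobody is lost.

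This rests on reading the t-test as patient-level, on two-sided testing, and on an ICC of 0.04 for the quantity tested. If the ICC is larger the error grows quickly, to about 21% at 0.20, the value that would reproduce the stated 240 patients. High power does not help, because it offers no protection under the null hypothesis. For the single indicators and CAT, the text is silent on the GP level, and the size of any error there is unknown.

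**What to change.** - **Primary outcome:** replace the t-test with a linear mixed model with a random intercept for GP and small-sample degrees of freedom (for example Kenward-Roger). A t-test on GP means is an acceptable simple version, with degrees of freedom equal to the GPs analysed minus 2 (28 if all 30 remain).
- **Binary indicators:** name the GP as the cluster in GEE, with a small-sample variance correction for about 30 clusters, or use mixed logistic regression with a random GP effect.
- **CAT:** replace repeated measures ANOVA with a mixed model that has both GP and patient levels.
- **ICC:** confirm which value the sample size used.

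The cost is analysis wording only; design, data collection and recruitment are unchanged. At the stated inputs the correct test keeps about 99% power. If the ICC were 0.20, power would be about 88%, slightly below the 90% target.
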